**B. Determination of efficacy against pneumonia in HIV-uninfected children**

To be included in the second primary efficacy calculations the case must meet the following criteria:

* Admission to hospital for pneumonia 14 days or more after the third dose of study vaccine.

* Have been vaccinated according to the protocol (see Section VI).

* Not have acquired or congenital immunodeficiency syndromes (HIV negative status determined by PCR for those with a positive HIV ELISA).

Patients enrolled in the study who require hospitalization will be categorized according to the following system, based on their clinical presentation.

**C. Clinical definition of cases**

**1. Hospitalized pneumonia**

This definition relates to efficacy against pneumonia as it will appear in the primary analysis. This is a radiological definition in recognition of the subjectivity of the clinical signs of pediatric pneumonia. The usual clinical signs, tachypnea, chest wall indrawing, fever, crepitations, and rhonchi can all be present in acute infections other than pneumonia. More specific auscultatory signs, such as bronchial breathing are not very sensitive and are unlikely to be found in the absence of striking radiological signs. Furthermore, children with definite radiological pneumonia without any of the usual clinical signs are found frequently and are generally regarded as having pneumonia. Radiological pneumonia will be defined as one or more of the following:

* definite lobar consolidation

* definite diffuse or non-lobar consolidation

* pleural fluid

All readings will be made by a pediatrician with experience in reading chest radiographs and no clinical information about the case. Only radiographs taken during the admission in question will be viewed, but all radiographs may be viewed. All cases positive by the above criteria will be confirmed by a second reader. If there is not agreement that a case is positive, it will be regarded as negative. When a child is discharged or dies, the radiographs will be set aside to be read at the next reading session. Reading sessions will take place every 2 weeks.

**2. Graded ARI definitions**

These definitions are intended for use in the secondary analyses, to determine the contribution of pneumococci of vaccine serotypes to various severities of ARI, and the efficacy of the vaccine for the prevention of various ARI syndromes.

**a. Acute lower respiratory infection - non severe**

Cough of less than 14 days duration associated with fast breathing ( >50/min in children less than one year of age and >40/min in children older than one year). No lower chest wall indrawing, respiratory distress, inability to drink, cyanosis, or desaturation (SaO2 < 90%). The child is not in need of admission for this problem alone.

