In the proposed study, vaccination with pneumococcal conjugate vaccine will be performed at all clinics providing routine immunization services in Soweto and Orange Farm [Appendix 3]. Vaccination will be performed by nurses trained in the administration of childhood immunization and who are specifically employed for this trial.

Surveillance for study patients admitted to Chris Hani Baragwanath Hospital will be done by study pediatricians and assistants in collaboration with the attending pediatricians at the hospitals.

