**3. Vaccine Efficacy**

The statistical methods for calculating the efficacy of the nonavalent pneumococcal conjugate vaccine are described in Section XII. Vaccine efficacy will bedefined as the number of cases of culture-confirmed invasive pneumococcal disease or pneumonia in the HIV-negative group receiving the pneumococcal conjugate vaccine compared to the number of cases occurring in the placebo group. The study pediatricians will conduct daily surveillance for cases of severe pneumonia, as defined in Section VIII, at Chris Hani Baragwanath Hospital. In addition, a list of all cases of culture-confirmed pneumococcal disease will be obtained daily from the hospital microbiology laboratories. HIV testing will be performed in an anonymous manner for all children with study outcomes who are not tested for HIV during hospitalization. Those outcome cases with no HIV test results will be excluded from the efficacy analyses.

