**d. Very severe pneumonia**

Any child with confirmed radiological pneumonia who also has hypoxemia (SaO2 < 90%).

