**C. Secondary efficacy outcome variables and statistical analyses**

The following efficacy outcome variables will also be evaluated for HIV-seronegative children. The analyses will include the graded ARI case definitions listed in VIII C.2. The primary outcomes (see above) and secondary outcomes 1 and 2 below will also be evaluated for children infected with HIV (see E below) as secondary analyses. The power for these analyses will depend on the number of outcome cases meeting the definition for inclusion in the particular analysis.

1. All invasive pneumococcal disease, including nonvaccine serotypes, in children who complete three doses of vaccine. This analysis will be performed using the methods and case definitions described above for the primary outcomes and include all first episodes of pneumococcal disease, regardless of serotype.

2. Vaccine-serotype invasive pneumococcal disease in children who complete at least two doses of vaccine, the first episode of disease occurring at least 14 days after the 2nd dose of vaccine. Exact binomial tests, including children who meet the case definitions described above and who have received either 2 or 3 doses of the vaccine, will be used as for the primary outcome analyses.

3. Vaccine-serotype invasive pneumococcal disease in all children who have received at least one dose of vaccine in the study regardless of immunization status (intent-to-treat analysis for vaccine-serotype pneumococcal disease). The intent-to-treat analysis will include the first episode of vaccine-serotype pneumococcal disease in children who were initially randomized into the study and received at least one dose of study vaccine and regardless of the number of vaccine doses they eventually received or whether they voluntarily withdrew from the study and were lost to follow-up. The null hypothesis of no difference between the two groups in all randomized chldren will be tested.

4. Vaccine immunogenicity will be assessed in a random sample of 400 children over the study period, or 200 children per lot of study vaccine introduced into the trial. The geometric mean titers of the antipneumococcal antibodies and 95% confidence interval of the vaccinated children will be determined and the distribution will be examined using reverse cumulative plots. The different response distributions of vaccine lots will be compared.

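### Non-severe acute lower respiratory infection falls within the secondary efficacy analyses, but cases are sought only among hospitalized children, so the trial cannot estimate efficacy against it

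*Protocol*

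**What the plan says.** Section VIII.C.2 of the protocol sets out four graded definitions of acute respiratory infection (ARI) for the secondary analyses. It gives them two uses: to describe how much vaccine-serotype pneumococci contribute to ARI of differing severity, and to determine "the efficacy of the vaccine for the prevention of various ARI syndromes". Section IX.C then commits the secondary efficacy work to them: "The analyses will include the graded ARI case definitions listed in VIII C.2". Neither section sets any grade apart.

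Grade (a), in Section VIII.C.2.a, is recent cough with fast breathing and no sign of severity. It ends: "The child is not in need of admission for this problem alone".

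On who is classified, Section VIII.B states: "Patients enrolled in the study who require hospitalization will be categorized according to the following system, based on their clinical presentation". On how cases are found, Section III states: "Surveillance for study patients admitted to Chris Hani Baragwanath Hospital will be done by study pediatricians and assistants". Section V.F.3, on vaccine efficacy, states: "The study pediatricians will conduct daily surveillance for cases of severe pneumonia, as defined in Section VIII, at Chris Hani Baragwanath Hospital".

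**The concern.** An efficacy estimate needs the outcome to be looked for in the whole randomized cohort, in the same way in both arms. Grade (a) is defined largely by the child not needing hospital care for it, while the only place where outcomes are looked for is the hospital. If the plan is followed as written, the report could carry a vaccine-efficacy figure labelled as protection against non-severe acute lower respiratory infection (ALRI), although the underlying cases are chance findings in children admitted for something else. The label would claim more than the data can show.

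**Working it through.** No arithmetic applies: the protocol gives no rate, expected count or power for non-severe ALRI. The check sets the definition, its use and each case-finding route side by side.

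1. **Use.** Sections VIII.C.2 and IX.C put the graded definitions, grade (a) included, among those used for secondary efficacy analyses.

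2. **Definition.** Grade (a) requires that the respiratory illness would not by itself lead to admission (Section VIII.C.2.a).

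3. **Efficacy case-finding.** Section VI.E.1 describes screening on arrival in the admission ward, daily review of the admitting-ward registers, and follow-up of children on the pediatric wards with a sterile-site pneumococcal isolate. Section V.F.3 adds daily surveillance for severe pneumonia and a daily laboratory list of culture-confirmed pneumococcal disease. None of these looks for a child with mild respiratory illness seen at a clinic or kept at home.

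4. **Other contact with participants.** Sections V.F.1 and VI.D provide for observation after vaccination and for parents to report reactions of concern; both serve safety. Section X asks outside doctors and nurses to note medical attendances on the Road to Health card, which is reviewed at vaccination visits or by the admitting physician. The three study-vaccine visits end with dose 3, before the primary outcomes' window of 14 days after dose 3 opens. The routine timetable in Section VI.B also lists visits at 9 and 18 months, but the protocol nowhere makes the card a source of ARI outcomes, and Section VI.E.1 says study physicians will not see it.

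5. **HIV status.** The study's HIV specimen is described under the investigation of hospitalized patients (Section VI.E.2), and the introduction to Section IX excludes outcome cases without an HIV result. No blood collection is described for a non-severe case seen outside hospital.

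6. **What a comparison of arms would measure.** Let λ be the rate of non-severe ALRI in an arm of the cohort (v = vaccine, c = placebo). The efficacy of interest is 1 − λ_v/λ_c. With equal allocation, the ratio of observed grade (a) counts is instead

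   [P_v(admitted for another problem) / P_c(admitted for another problem)] × [P_v(grade (a) present, given such admission) / P_c(grade (a) present, given such admission)].

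   This equals λ_v/λ_c only if the first factor is 1 and the second matches the ratio in the cohort. The first factor is doubtful, because the vaccine is meant to prevent some of the other admissions, pneumococcal meningitis for example. The second concerns only children ill enough to be in hospital for another cause. The protocol states neither condition, and without outpatient data neither could be fully checked.

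**The case against.** The best defence is that grade (a) was never meant to describe community illness. Section VIII.B confines the whole classification to children who require hospitalization, and the closing words of the grade (a) definition fit a child admitted for a different reason. On that reading it is a coherent residual label. The objectives in Section II.B list nothing on non-severe ALRI, and Section IX.C says only that the analyses will include the graded definitions, without promising an estimate for each. An SAP, which is not at hand, could settle which grades receive one.

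Much of this stands. The category need not be empty, and the efficacy claim for grade (a) follows from general wording, not from a named objective. It does not remove the problem. As a residual label, grade (a) is usable for description, but Sections VIII.C.2 and IX.C still place it among definitions used for efficacy without exception. An SAP could drop the estimate, but it could not recover episodes that the surveillance never collected.

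**Conclusion.** The point holds as a mismatch between one secondary outcome and the surveillance. Grade (a) cases would be seen only incidentally, and a comparison of arms on them would not estimate efficacy against non-severe ALRI. This rests on reading Sections VIII.C.2 and IX.C as covering all four grades, and on there being no outpatient ARI surveillance beyond what the protocol describes. One of four graded definitions is affected. Invasive disease, hospitalized radiological pneumonia and the case-driven sample size are not, so the priority is modest.

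A reader might infer more than the protocol supports:

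- **That a capture rate can be read from Appendix 1.** It gives diagnoses for ward admissions in 1995. It does not describe trial participants, and it says nothing about how often cough with fast breathing accompanies another illness.
- **That the overlap of the severe and very severe grades is a fault.** A more severe category nested in a less severe one is an ordinary cumulative endpoint. The protocol does not call the grades mutually exclusive and plans no test for a severity gradient.
- **That a null result for grade (a) would be taken to show protection against severe disease only.** Nothing in the protocol points to that interpretation.

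**What to change.** In Section IX.C, state that the graded definitions enter the efficacy analyses except for non-severe ALRI. In Section VIII.C.2.a, state that this grade is recorded and reported descriptively, by arm, among children hospitalized for another reason. The other three grades can stay as written.

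The change needs wording only, with no new data, visits or tests. The sponsor gives up an efficacy estimate for non-severe ALRI that hospital-based surveillance could not support.

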**b. Severe pneumonia**

Cough of less than 14 days duration with any one of the following: indrawing of the lower chest wall (subcostal retractions) in well-nourished children and/or intercostal retractions in malnourished children, respiratory distress, inability to drink, cyanosis or desaturation (SaO2 <90%), *and* with a chest radiograph positive for pneumonia by the above criteria.

**c. Severe acute lower respiratory infection**

Any child whose primary symptom is cough of less than 14 days duration and who is judged on clinical ground to require admission to hospital. Acute laryngotracheobronchitis (croup) and other severe upper respiratory tract infections are excluded from this category.

**d. Very severe pneumonia**

Any child with confirmed radiological pneumonia who also has hypoxemia (SaO2 < 90%).

**3. Pneumococcal pneumonia**

A diagnosis of pneumococcal pneumonia will be made if the child fulfils the above clinical and/or radiological criteria and if *S. pneumoniae* is isolated from blood or pleural fluid.

**4.**  **Pneumococcal meningitis**

Pneumococcal meningitis will be diagnosed if *S. pneumoniae* is isolated from CSF and/or if, in addition to the following clinical criteria, pneumococci are isolated from blood or the latex agglutination test on CSF is positive for pneumococci.

* CSF neutrophil count of >5 cells\ ml, and

* total CSF protein of >0.5 g\l, and

* CSF glucose <50% of blood glucose level

**5. Other invasive pneumococcal disease**

These will include the following diagnoses based on isolation of *S. pneumoniae* from blood and/or relevant normally sterile body fluids:

**a. Pneumococcal peritonitis**

The presence of abdominal tenderness and guarding in a child with purulent ascitic fluid.

**b. Pneumococcal septic arthritis**

The presence of clinical signs of joint inflammation and purulent synovial fluid.

**c.** **Pneumococcal cellulitis**

Inflammation of subcutaneous tissue.

**d.** **Pneumococcal septic shock without a focus**

The presence of fever, tachycardia coupled with abnormal responsiveness, and/or hypotension, and/or dehydration, and/or metabolic acidosis (pH <7.25)

.

**IX. Sample size and plan for analyses**

The study is designed primarily to evaluate the impact of the nonavalent pneumococcal conjugate vaccine in HIV-uninfected children. The cases in HIV-infected children will not be included in any primary analyses of vaccine efficacy as their outcome variables, disease incidence rates, expected vaccine efficacy, and expected follow-up time may all be different from that in the general population. The impact of the vaccine in this special population will be evaluated separately as a secondary objective. All case ascertainment will include HIV testing, in an anonymous and confidential manner. The HIV status will only be linked to clinical outcomes at the time of analysis. It will not be linked to any other health record of the child. Outcome cases for which HIV results are not available will be excluded from analyses.

**A. Primary outcome variables**

1. Cases (see Section VIII for case definition) of vaccine-serotype pneumococcal invasive disease in children who have completed the three-dose series per protocol.

2. Cases (see Section VIII for case definition) of radiologically-confirmed hospitalized pneumonia in children who have completed the three-dose series per protocol.

Outcomes will qualify for the primary analysis of they occur at least 14 days after the third dose of vaccine/placebo. Outcome ‘1' will be the basis for the vaccine efficacy estimate. Since the prevalence of radiographically-confirmed severe pneumonia may be several-fold higher than that of culture-confirmed pneumococcal invasive disease (to be estimated from the ongoing pneumonia surveillance study) and the mortality rate from severe pneumonia is probably high (to be estimated from the ongoing pneumonia surveillance study), outcome ‘2' will be used to assess the effectiveness of the vaccine in reducing the overall pneumonia disease burden and its impact on public health as well as to estimate the proportion of severe pneumonia caused by pneumococci of vaccine serotypes.

**B. Statistical analyses for the primary outcome variables**

Efficacy of the vaccine will be estimated by comparing the incidence rates of vaccine-serotype invasive pneumococcal disease (Primary Outcome ‘1') between the recipients of three doses of the vaccine and placebo. Efficacy will be estimated as (1-RR) x 100%, where RR is the ratio of the incidence rate of the treated group versus that in the control group. With individualized randomization of a large cohort at a 1:1 allocation ratio, the follow-up time in the treated and control groups should be equal. The rate ratio can, therefore, be estimated as the ratio of the number of cases in the treated group versus that in the control group.

An exact two-sided 95% confidence interval for vaccine efficacy will be estimated, based on the binomial distribution for the number of cases among vaccinees, given the total number of cases and the ratio of follow-up time in placebo recipients to follow-up time in vaccine recipients. The statistical power for this analysis depends on the true efficacy and the number of accrued cases. For power calculations, we assume the true efficacy against vaccine-serotype invasive disease is 70% and that the ratio of follow-up times is 1. Then 28 cases are required for an 80% probability that the lower limit of the 95% confidence interval for efficacy will be greater than 0 (i.e., to reject the hypothesis of no efficacy); for an 80% probability that the lower limit will be greater than 20% 43 cases are required. We plan to enrol study infants until 28 HIV-uninfected vaccine-serotype cases have been accrued for the primary analysis and then continue surveillance until a total of at least 43 cases have been accrued. The following cases splits, out of the 28 cases, can lead to rejection of the null hypothesis.

| Control Cases | Treated  Cases | Estimate of vaccine  efficacy (%) | Lower 95% Confidence  Limit of VE (%) |
| --- | --- | --- | --- |
| 28 | 0 | 100 | 85.9 |
| 27 | 1 | 96.3 | 77.5 |
| 26 | 2 | 92.3 | 69.2 |
| 25 | 3 | 88.0 | 60.6 |
| 24 | 4 | 83.3 | 51.4 |
| 23 | 5 | 78.3 | 41.5 |
| 22 | 6 | 72.7 | 30.6 |
| 21 | 7 | 66.7 | 18.6 |
| 20 | 8 | 60.0 | 5.1 |

The current estimate of the incidence of invasive pneumococcal disease in children under the age of 2 years in Soweto is 160/100,000 child years [12]. Assuming that 70% of the disease cases are due to the vaccine serotypes, the vaccine-serotype disease rate is 112 cases per 100,000 child years. Based on this estimate of disease rate and the assumption that the true vaccine efficacy is 70%, approximately 19,231 child years follow-up per treatment group will be needed to accrue 28 cases of vaccine-serotype disease in HIV-uninfected children. The annual birth cohort in Soweto is approximately 24,000 infants, 4% (960) of whom would be expected to be HIV-infected. Allowing for loss to follow-up, the entire birth cohort over a two year period will be recruited to reach the targeted enrolment goal. The study is expected to accrue 28 cases of vaccine-serotype disease in HIV-uninfected children in approximately 32 months. Approximately 29,533 child years of follow-up per treatment group, expected in approximately 39 months, will be needed to accrue 43 cases. A more accurate estimate of the disease rate is expected to be obtained prior to the start of the study from the prospective cohort study currently underway in Soweto.

The rate of hospitalized pneumonia (Primary Outcome ‘2') will be compared between the treated and the control group using a Poisson regression, with age category and calendar month of the third dose (season category) as possible stratification variables. An estimate of the rate reduction and its confidence interval will be obtained from the Poisson regression. Multiple events of an individual will be included in the rate estimates. The null hypothesis is that there is no rate reduction and will be tested based on the Poisson regression with a two-tailed  = 0.05. An analysis to compare the number of children with at least one event between the two groups will also be performed.

The statistical power for the analysis of pneumonia (Primary Outcome ‘2') depends on the incidence rate in the control population and the reduction of the rate in the vaccinated population. Once a reliable estimate of the disease rate becomes available from the prospective cohort study, detailed power calculations for this outcome variable will be provided. However, since the disease rate is expected to be substantially higher than the rate for vaccine-serotype invasive disease, it is expected that by the time 28 cases of serotype-specific invasive disease are accrued, the study cohort will be enough to provide an excellent statistical power to detect a clinically significant reduction in the rate of severe pneumonia.

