**E. HIV-positive population**

It is estimated that 4% of the annual birth cohort (approximately 900 children) in Soweto will be HIV-seropositive. The effect of the vaccine on the following outcome variables in children enrolled in the study who are confirmed to be HIV-infected will be evaluated.

1. Vaccine-serotype invasive disease. The analysis will include the comparison of disease rates and time to first episode of disease (from 14 days after the third dose of vaccine) between the vaccinated and control children. A sensitivity analysis will be performed to examine the robustness of the vaccine efficacy estimate with respect to the assumption of equal follow-up time in the two groups.

2. Radiologically-confirmed hospitalized pneumonia. The analysis will include the comparison of event rate and time to first event between the two groups. An analysis to compare the number of children with at least one event will also be performed.

3. All invasive pneumococcal disease, including nonvaccine serotypes. The analysis will be done as described in Section IX.C.1 above.

4. Pneumonia-related mortality. Mortality resulting from pneumonia will be analyzed using the life table method and the survival curves of the vaccinated and the control group will be compared using the log rank test.

5. All cause mortality. The all-cause mortality will be analyzed using the life table method and the survival curves of the vaccinated and the control group will be compared using the log rank test.

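### The primary efficacy estimate may be taken from bare case counts while its exact interval uses the follow-up-time ratio, so the two can diverge slightly in a per-protocol set formed after randomisation

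*Protocol*

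**What the plan says.** Section IX.B of the protocol sets efficacy at (1 − RR) × 100%, "where RR is the ratio of the incidence rate of the treated group versus that in the control group". It then reasons that, with individual 1:1 randomisation of a large cohort, "the follow-up time in the treated and control groups should be equal", and draws the consequence: "The rate ratio can, therefore, be estimated as the ratio of the number of cases in the treated group versus that in the control group". The Protocol Summary and section V.F.3 also describe efficacy through case numbers, the latter as cases in the vaccine group "compared to the number of cases occurring in the placebo group".

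The next paragraph of IX.B turns to the interval, which is to be exact, binomial and two-sided at the 95% level. Its calculation is conditional, namely "given the total number of cases and the ratio of follow-up time in placebo recipients to follow-up time in vaccine recipients". For the power calculation only, "we assume the true efficacy against vaccine-serotype invasive disease is 70% and that the ratio of follow-up times is 1". The table of rejecting splits of 28 cases follows in that same paragraph.

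Sections VIII.A and IX.A restrict the first primary outcome to children vaccinated with three doses per protocol, with disease at least 14 days after the third dose. For HIV-infected children, section IX.E adds: "A sensitivity analysis will be performed to examine the robustness of the vaccine efficacy estimate with respect to the assumption of equal follow-up time". No such check is stated for the primary analysis.

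**The concern.** The point estimate and the interval agree only when the two arms contribute equal follow-up. The interval takes the follow-up ratio as an input; the count-based estimate does not.

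The reason given for dropping the ratio is randomisation, but randomisation balances the children randomised. The primary set is formed later, once three doses have been completed on schedule. Before then children can leave through a contraindication after a reaction or parental withdrawal (IV.D), or be excluded for a wrong vaccine code (VI.B, item 5). Reactions can depend on arm. Equal child-time in this set is therefore likely in a blinded trial, but it is an empirical matter and not a consequence of the allocation.

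At stake is a headline efficacy figure that would not be the incidence-rate quantity the protocol defines and would not match the interval printed beside it. The wording also leaves a choice between two estimators open until after unblinding.

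**Working it through.** **Inputs.** From IX.B: RR as a rate ratio, 1:1 allocation, true efficacy 70%, r = 1 for power, 28 and 43 cases, and the table of splits. From section III: 98% three-dose compliance in the Phase II study. The realised r (placebo child-time ÷ vaccine child-time) is not in the documents, so values from 0.95 to 1.10 are assumed.

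**Formulas.** Given N cases in total, the number x in the vaccine group is binomial with p = RR/(RR + r), so RR = r × p/(1 − p). Then:

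- count-based efficacy = 1 − x/(N − x)
- rate-based efficacy = 1 − r × x/(N − x)
- lower limit = 1 − r × u/(1 − u), where u is the exact (Clopper-Pearson) upper 97.5% limit for p.

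**Step 1: the plan's own figures at r = 1.** With p = 0.3/1.3, power is 82.2% at 28 cases (lower limit above 0) and 82.6% at 43 cases (lower limit above 20%), consistent with the stated 80%. All nine point estimates in the table match, and all lower limits agree within 0.1 point. For 20:8, u/(1 − u) = 0.948, giving 5.2% against the printed 5.1%. The 19:9 split gives −9.9%, so 20:8 is indeed the last rejecting split.

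**Step 2: r away from 1.** The count-based estimate stays at 60.0% (20:8) and 72.7% (22:6) throughout.

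| r (assumed) | 20:8, rate-based efficacy (lower limit) | 22:6, rate-based efficacy (lower limit) |
| --- | --- | --- |
| 0.95 | 62.0% (9.9%) | 74.1% (34.1%) |
| 0.98 | 60.8% (7.1%) | 73.3% (32.0%) |
| 1.00 | 60.0% (5.2%) | 72.7% (30.6%) |
| 1.02 | 59.2% (3.3%) | 72.2% (29.3%) |
| 1.05 | 58.0% (0.5%) | 71.4% (27.2%) |
| 1.10 | 56.0% (−4.3%) | 70.0% (23.7%) |

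The slope is x/(N − x): 8/20 = 0.40 efficacy points per 1% imbalance at 20:8, and 6/22 = 0.27 at 22:6.

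**Step 3: what the count estimator targets.** At a true efficacy of 70% it targets 1 − 0.3/r: 68.4% at r = 0.95 and 71.4% at r = 1.05. The error has no fixed direction.

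**Step 4: the rejection decision.** The 20:8 lower limit reaches zero at r = 1/0.948 = 1.055. At 43 cases, the 31:12 split has a lower limit of 22.5% at r = 1 and falls to 20% at r = 1.032. Both crossings occur inside the planned interval, which takes r as an input. They show the interval working as intended.

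**Step 5: how large r could plausibly be.** If vaccine recipients completed three doses at 98% and placebo recipients at 100%, r = 1/0.98 = 1.02 and the 20:8 estimate moves from 60.0% to 59.2%. If 98% were the pooled figure and every non-completer were in the vaccine arm, r = 1/0.96 = 1.042. Efficacy would then be 1 − 0.4 × 1.042 = 58.3%, with a lower limit of 1 − 1.042 × 0.948 = 1.2%, still rejecting. Both are deliberately one-sided cases, and they cover dose completion only, not later follow-up.

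**The case against.** The best defence is that nothing is contradictory. Efficacy is defined on incidence rates, the count ratio is offered as something that can be used because follow-up should be equal, and the interval is the general form that reduces to the same thing at r = 1. If follow-up proves unequal, the definition should govern, and an analysis plan could settle the detail. This stands as far as the estimand goes. It does not remove the point: IX.B states the count ratio without a condition on observed follow-up, and the Summary and V.F.3 repeat the count comparison.

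A material imbalance is also unlikely. The trial is double-blind with a placebo of identical appearance, wrong-code errors are described as rare, and Phase II compliance was 98%. This stands and limits the size.

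A third objection is that child-time from all per-protocol children includes HIV-infected children, whose survival vaccination might affect. With 4% infected (IX.B) and 50% dying in the first year (IX.F), deaths spread evenly over one year and confined to one arm would remove about 0.04 × 0.5 × 0.5 = 1% of a year's child-time. That is a real limitation, but the planned interval already carries it.

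Three stronger readings are tempting and not supported:

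- That the test of efficacy is compromised: it is not, because the interval uses r.
- That the table of 28-case splits hides its assumption: the same paragraph states a follow-up ratio of 1 before the table.
- That the sensitivity analysis reserved for HIV-infected children is inconsistent: section IX says their expected follow-up may differ and IX.F expects half to die in the first year, so the different treatment is reasoned. It shows only that the protocol regards equal follow-up as an assumption.

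**Conclusion.** The point holds as a minor mismatch in the stated primary estimator. The estimate may be taken from raw counts on a justification that does not fully cover a set selected after randomisation, while its interval uses actual follow-up. Only the point estimate is exposed, by about 0.4 efficacy points per 1% imbalance at 20:8 and less at more favourable splits, upwards or downwards. If r lies within 1–2% of 1, which the design makes likely but the documents cannot establish, the discrepancy is under one efficacy point. A reader might infer that counts systematically favour the vaccine; the documents give no evidence of differential loss, and r below 1 would understate efficacy.

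**What to change.** In IX.B, replace the count-ratio sentence with: RR is estimated as (vaccine cases ÷ placebo cases) × (placebo child-time ÷ vaccine child-time), using per-protocol child-time from 14 days after the third dose, and the same ratio enters the exact interval. Report the raw count ratio only as a check, and align the efficacy descriptions in the Summary and V.F.3.

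The cost is wording, since the interval already requires the child-time ratio. There is one small downside to state openly. HIV testing is planned for outcome cases or hospitalised children and for the immunogenicity subset, so the status of most non-cases is unknown. Child-time must therefore cover all per-protocol children, including the roughly 4% expected to be HIV-infected.
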